### Interventions

#### Development

The intervention content is based on earlier published research of the authors [17, 18] and qualitative research conducted within the development process of this study. This qualitative research consisted of focus groups with generalist physical therapists, occupational therapists and exercise therapists (total participants = 16); focus groups with physical therapists, occupational therapists and exercise therapists specialised in occupational health, and with other relevant healthcare providers involved in occupational health (total participants = 22); and focus groups with patients from the target population of the intervention (total participants = 18). The results of these focus group studies will be published elsewhere. The intervention was developed by the first two authors, in cooperation with the other authors of this publication. All members of the advisory group had the opportunity to comment on the development and content of the intervention.

#### Control group

Physical therapy practices randomised to the control group will provide regular physical therapy (according to the existing guidelines) to their patients. These patients will be asked to participate in the study and to fill in the baseline and follow-up questionnaires.

#### Intervention group

Physical therapy practices randomised to the intervention group will provide regular physical therapy (according to the existing guidelines). In addition, they are able to use all the ‘WORK TO BE DONE’ intervention components and materials. These invention components and materials are:

##### Symposium

At the start of the intervention, a full-day symposium will be held with presentations about the importance of work-focused healthcare, information about the trial and collaborating with other occupational health professionals. There will also be a three-hour masterclass about shared decision-making. The symposium will be video recorded for physical therapists who are unable to attend the symposium.

##### E-learning

Physical therapists must follow an e-learning course consisting of two parts. The first part contains general information about the importance of work-focused healthcare, the interaction between work and health, and (work-related) factors influencing participation in work. The second part contains more specific information and guidance about addressing patients’ work participation in the diagnostic and treatment phase and about working with occupational health professionals, including guidance on cooperation between generalist physical therapists and physical therapists specialised in occupational health.

##### Online toolkit

Physical therapists can use an online toolkit to easily find information about providing work-focused care. Using the keyword search functionality, they can find information about laws and regulations, assessment and other tools, questionnaires, and occupational health professionals. Moreover, the toolkit contains short information about all the topics covered in the e-learning course.

##### Network

Physical therapists will be part of a local network through which they can easily contact occupational health physical therapists, exercise therapists specialised in occupational health, and occupational therapists with additional training in occupational health.

##### Patient information

Physical therapists can use patient information developed by the authors highlighting the importance of work-focused healthcare.

#### Co-interventions

No restrictions with regard to co-interventions will be set. Both the intervention group and the control group will be allowed to use all other interventions (co-interventions). We will ask for participation in co-interventions in the follow-up measurements.

### Outcome assessment and data collection

All outcome measures will be self-reported measures. Data will be collected using online questionnaires filled in by the participating patients at the start of the intervention (T0), four months after the start of the intervention (T1, short-term effects) and eight months after the start of the intervention (T2, long-term effects). All questionnaires will be developed using Qualtrics online survey software (Qualtrics®). Outcome measures will be collected from the patients. The schedule for enrolment, outcome measures and time points is summarised in Table 1. Physical therapists will be asked to fill in a questionnaire at the start of the intervention and after eight months.

**Table 1 Tab1:**
[figure not shown]
Schedule for enrolment, outcome measures and time points.

#### Descriptive data

Characteristics of the patients will be collected at baseline in the first questionnaire. Patient characteristics include age, gender, education, family status, area of complaints, duration of complaints, profession and work/workplace, and hours of employment.

Characteristics of the physical therapists will be collected at baseline with the first questionnaire. Physical therapist characteristics include age, gender, education, area of specialisation and years of experience as a physical therapist.

#### Primary outcomes

##### Limitations in specific work-related activities

The limitations in specific work-related activities in the previous week will be assessed using a patient-specific functional scale (PSFS) [26, 27]. Patients will be asked to identify the most important work-related activity they are unable to perform or are having difficulty with as a result of their musculoskeletal problems. Patients will be asked to rate each activity on an 11-point scale indicating the current level of difficulty associated with each activity. The PSFS is a valid, reliable and responsive outcome measure for patients with MSDs [26, 28–30]. As the minimal clinically important difference (MCID) we will use two points [31–34].

##### Pain during work

The level of pain experienced by the patient in the previous week during work will be assessed using the 11-point numeric pain rating scale (NPRS). The NPRS has been established as reliable and valid [32, 35–37]. The MCID of the NPRS in patients with musculoskeletal complaints is two points [32–34].

#### Secondary outcomes

**Limitations in general work-related activities** will be assessed using a single question about the limitations experienced during work in general due to the complaints (11-point scale) [38].

**General pain**. The general level of pain experienced by the patient in the previous week will be assessed using the 11-point numeric pain rating scale (NPRS).

**Quality of life** will be assessed using the 12-item Short-Form Health Survey (SF-12) [39].

**Presenteeism** will be assessed using the Dutch version of the 6-item Stanford Presenteeism Scale (SPS-6) [40].

**Absenteeism** will be measured by asking the patient the number of days they had been out of work due to their complaints during the previous month.

**Estimated risk for future work disability** will be assessed using the Örebro Musculoskeletal Pain Screening Questionnaire (short form) [41].

**Work-related psychosocial risk factors** will be assessed using the blue flags questionnaire [42].

The degree to which health problems interfere with specific aspects of **job performance** and the **productivity impact** of these work limitations will be assessed using the Work Limitations Questionnaire [43].

**Work ability** will be assessed using the Work Ability Index-Single Item Scale (WAS), which is a responsive measure for work participation and highly predictive for future sickness absence [44].

The amount of **attention to work participation** given by the physical therapist, and the **level of satisfaction** of the patient with this attention will be measured using five-point Likert scales.

#### Other measures include

In addition, we will collect data on the attitude towards addressing work participation in physical therapy practice (five-point Likert scale), the use of other healthcare interventions (co-interventions), the number of physical therapy treatment sessions, recurrences of complaints and referrals to other occupational health professionals (including physical therapists specialised in occupational health). All participating physical therapists (in the intervention arm as well as the control arm) will receive a questionnaire about their awareness, attitude, knowledge, and self-efficacy with regard to the treatment of working patients with MSDs at T0 and T2. Information about their work experience with the intervention and the use of the intervention materials will be collected at T2 (intervention group only).

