### Randomisation and blinding

The physical therapy practices of the participating physical therapists will be the unit of randomisation (cluster). Each practice will be randomly assigned to either the intervention or control arm on a 1:1 basis. The allocation sequence will be generated online (with a block size of six) [25] using http://randomization.com by the principal investigator. Participating practices will be randomised in the order that they confirm their participation in the study. The practices will be informed about the group allocation by the principal investigator. Based on the randomisation, physical therapists working in the randomised practices will be able to use all the ‘WORK TO BE DONE’ intervention components (intervention group) or will continue providing regular physical therapy to their patients (control group). Physical therapists and patients cannot be blinded to allocation group.

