### Procedures

As soon as a physical therapy practice confirms participation in this study, they will receive an email from the principal investigator indicating to which group they have been allocated. All participating physical therapists will receive patient information about the study and materials needed for the inclusion of patients. Patients will be recruited and informed by the participating physical therapy practices. Consecutive patients will be asked if they are willing to participate in this study and will receive the information letter. Patients will be allowed to use all the time they need to consider their participation. As soon as a patient has decided to participate, the first consult will be planned. Patients will also receive an information letter and will be given the time they need to consider their participation. If patients do not want to participate in the study, they will receive regular physical therapy treatment and will not be enrolled in the study. If patients want to participate in the study, the physical therapist will assess them for eligibility during the intake and ask for written informed consent and their contact details. The physical therapist will then send the contact details to the investigators via a secured app (Siilo, Siilo Holding B.V., the Netherlands). An image of the informed consent form will also be sent to the investigators via a secured app. The original form will be sent by regular mail or will be collected by the investigators.

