## Discussion

This CRCT will investigate to what extent integrating work-related factors in the care processes of generalist physical therapists and improving the cooperation between generalist physical therapists and physical therapists specialised in occupational health will enhance the effectiveness of physical therapy (in primary healthcare) for working patients with MSDs. Our hypothesis is that the intervention will result in better patient health and an increase in the knowledge of generalist physical therapists regarding work participation and the relevant factors that influence work participation, which will make it easier for them to integrate work participation into care and to decide when referral to or consulting with a physical therapist specialised in occupational health or another occupational health professional is appropriate.

After participating in this trial, generalist physical therapists delivering the ´WORK TO BE DONE` intervention will have increased their knowledge and will have integrated work-related factors in a structural and process-oriented way into their care processes. They will be better able to treat work-related and work-relevant complaints, resulting in less overtreatment. In addition, overtreatment will be reduced as generalist physical therapists will refer patients at an earlier stage to a physical therapist specialised in occupational health or another occupational health professional within the network.

For the patients, the trial is expected to result in faster recovery (pain and limitations in activities) and a higher quality of life. In addition, we expect that patients will have less absenteeism and be less limited in work-related activities.

The trial is expected to result in a more effective physical therapy process for working patients with MSDs. This will mean a substantial reduction of costs: lower costs thanks to a more effective physical therapy process and lower costs due to less or shorter sick leave and lower presenteeism. A process evaluation will be carried out which will provide insights in the facilitators and barriers with regard to implementation of the intervention.

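### Therapists give their baseline ratings of knowledge, attitude and self-efficacy after they have been told their arm, so T0 is not an allocation-free baseline for the therapist measures

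*Protocol article*

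**What the plan says.** All places are in the Protocol article.

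- **Randomisation and blinding:** "Participating practices will be randomised in the order that they confirm their participation in the study". The same section states that "Physical therapists and patients cannot be blinded to allocation group".
- **Procedures:** once a practice confirms, "they will receive an email from the principal investigator indicating to which group they have been allocated".
- **Outcome assessment and data collection:** "Physical therapists will be asked to fill in a questionnaire at the start of the intervention and after eight months".
- **Other measures include:** the therapist questionnaire goes to both arms and covers awareness, attitude, knowledge and "self-efficacy with regard to the treatment of working patients with MSDs at T0 and T2".
- **Symposium** (intervention arm): "At the start of the intervention, a full-day symposium will be held".
- **Discussion:** the hypothesis includes "an increase in the knowledge of generalist physical therapists regarding work participation". The Background states a similar hypothesis and presents greater knowledge as the route to better care.

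**The concern.** A baseline is useful for measuring change, or as a covariate, because allocation cannot have influenced it. Here the therapist baseline is a self-report on attitude, confidence and knowledge, given by people who already know whether they will be trained. Those assigned to training may rate themselves lower, because they expect to learn, or higher, because they are already engaged with the topic. Controls may react to not being chosen. If any training content has been seen by then, part of the effect is already in the baseline.

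At stake is the therapist-level part of the hypothesis. This questionnaire is the only measure of therapist knowledge that the article describes in both arms at two time points. If the patient outcomes show no difference, these data would help to separate training that did not change therapists from changed therapists who did not change patient outcomes. A baseline affected by allocation makes that distinction harder to draw.

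**Working it through.** No figure in the protocol depends on this point, so there is none to reproduce. The check is the order of events, followed by an illustration on assumed values.

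**Order of events**

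1. The practice confirms participation (Procedures).
2. It is randomised, in order of confirmation (Randomisation and blinding).
3. It is emailed its arm once it has confirmed (Procedures).
4. Therapists complete the first questionnaire when the intervention starts (Outcome assessment and data collection). It is labelled T0 under Other measures.
5. The symposium is also placed at the start of the intervention (Symposium).

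The start of the intervention can be read in two ways. If it is the trial-level start, T0 falls around the time of the symposium. If it is the start for the first patient, T0 would be expected after the training. Under both readings step 4 comes after step 3, so knowledge of the arm at T0 follows from the text. The order of steps 4 and 5 does not: no section says which comes first. The Descriptive data section says only that therapist characteristics are collected at baseline with the first questionnaire, which fits either order.

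**What a shifted T0 would do**

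Let D be the true between-arm difference in therapist score at T2, b the between-arm difference at T0 caused by knowing the arm or by early training, and r the within-arm slope of T2 on T0.

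- Change-score contrast: D - b.
- Baseline-adjusted contrast: about D - r × b.
- T2-only contrast: D, because T0 is not used.

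If b comes from knowledge of the arm, its sign is unknown. A positive b understates the effect and a negative b overstates it.

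If b is early training gain, write b = f × D, where f is the share of the gain already present at T0. The share of the effect kept is then 1 - f for the change score and about 1 - r × f for the adjusted contrast. The documents give neither f nor r; the values below are assumptions.

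| f | Change score | Adjusted, r = 0.3 | Adjusted, r = 0.5 | Adjusted, r = 0.7 |
|---|---|---|---|---|
| 0.10 | 90% | 97% | 95% | 93% |
| 0.25 | 75% | 92.5% | 87.5% | 82.5% |
| 0.50 | 50% | 85% | 75% | 65% |

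Example for f = 0.50 and r = 0.7: 1 - 0.7 × 0.50 = 0.65.

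**Reach**

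The planned number of practices is 17 per arm, 34 in total (Sample size). The stated order applies to participating therapists in all of them.

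**The case against.** The strongest reply has four parts.

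- **The finer timing may be elsewhere.** Figure 1 and Table 1 are not shown, and the full protocol is said to be on a public repository. Whether the form goes out before or after the symposium is detail that an article may leave to those sources. This stands, and for that reason training contamination is put only as a possibility. It does not remove the main point, because the article itself states the timing of the allocation email and of the questionnaire.
- **No analysis of therapist scores is set out.** The Data analyses section describes outcomes at T1 and T2, adjusted for baseline, while therapists are measured only at T0 and T2. This also stands: the bias arises only if T0 is used as a baseline. Measuring the same items in both arms at T0 and T2 does invite that use.
- **The measure is ancillary.** It is listed among other measures, and the research question concerns effectiveness for patients. This is correct and limits the weight of the point.
- **The remedy is not free.** Practices are randomised, but individual therapists fill in the form, so one slow therapist could delay a whole practice. This is fair and is met by a cut-off.

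Three stronger readings are tempting, and the document supports none of them. A reader might infer that T0 is completed at or after the symposium; the two sections share a loose phrase and give no order. A reader might infer that any early gain is lost one-for-one, so that the trial could show half the true gain; that needs a change-score analysis, which no section plans, and an assumed share of one half. A reader might infer that the therapist comparison is lost altogether; the T2 comparison does not use T0.

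**Conclusion.** The point holds in a limited form. By the article's own sequence, therapist self-ratings at T0 are recorded with the arm known, for a measure tied to the stated hypothesis. That they also follow some training is possible but not established.

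The consequence is potential bias in a T0 to T2 change or a baseline-adjusted comparison of therapist scores. Knowledge of the arm could push it either way, and training gain already in T0 would push it towards understatement. The size is unknown; the percentages in the table rest wholly on assumed f and r. The primary and secondary patient outcomes are untouched. This is a minor, avoidable weakness in an ancillary measure.

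The conclusion assumes that the unseen figure, schedule table and full protocol do not place a therapist questionnaire before the allocation email. If they do, the text should say so and the point falls.

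**What to change.** Send the therapist T0 questionnaire to both arms when the practice confirms, and collect it before the allocation email is released. Set a short cut-off, so that one slow therapist does not hold up a practice. In any case collect it before any symposium or e-learning content is seen. State this order in the protocol. Practices can still be randomised in order of confirmation; only disclosure waits.

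Where this is no longer possible, compare the arms on therapist scores at T2, and do not treat or present T0 as a pre-randomisation baseline.

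The cost is a short delay in telling practices their arm, and some follow-up of therapists who have not replied. The fix does not change the fact that therapists also know their arm at T2.

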### Sample size

The sample size was calculated based on the main outcome measures (11-item NPRS and 11-point PSFS), an expected effect size of 0.7 and a standard deviation of 1.8 [32, 45–47]. On the basis of two-sided testing, significance level of 0.05, power 0.8, accounting for the cluster design effect, assuming an ICC coefficient of 0.05, and 15 clusters per intervention arm, an effective sample size would require 10 patients per cluster (i.e. per physical therapy practice). With respect to the effect of cluster size variation, we added 10% additional clusters (in total 17 clusters per arm) [48]. Allowing for a 25% loss to follow-up, we would need to recruit 13 participants (i.e. patients) per cluster [49]. In total, we need to include 221 patients in each arm (442 in total).

### Data analyses

Analysis of the two groups will be conducted blinded to the treatment allocation and the data will be analysed according to the intention-to-treat principle. Baseline characteristics of the participants will be presented in means and standard deviations (symmetrically distributed continuous variables), median interquartile ranges (other continuous variables), and counts and percentages (categorical variables), and will be checked for baseline differences between the two groups.

All outcome measurements will be continuous variables and will be presented as means and standard deviations. Normality of the data will be checked and verified using histograms, normal probability plots and Shapiro-Wilk tests. Between-group differences for all outcomes will be analysed using linear regression. If data appears to be not normally distributed, Mann-Whitney U tests or log transformation will be performed.

Each outcome variable will be analysed independently at T1 and at T2 [50] as a dependent variable using the study group as an independent variable, adjusted for the baseline measurement of each outcome measure. Adjustment for confounding will only be applied if the regression coefficient of the intervention variable changes by more than 10% when the potential confounding variable is added to the model. If missing data for an outcome is > 5%, multiple imputation will be conducted. Results will be considered significant if p < 0.05. All analyses will be performed using IBM SPSS Statistics 26 (IBM Corporation).

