### Participants and recruitment

Participating physical therapy practices will be recruited from among legally registered physical therapists in the Netherlands. Physical therapists in the recruited physical therapy practices can participate in this study if they treat patients with MSDs and do not have a recognised specialisation in the area of occupational physical therapy or work-related physical therapy. Physical therapists will be recruited via announcements made by the stakeholders involved in newsletters and on websites, and via social media.

Patients will be recruited by the participating physical therapists. In order to be eligible for participation in this study, a patient must meet all of the following criteria:
Display one or more musculoskeletal complaintsHave an indication for physical therapy treatmentHave an employment contract or be self-employed (normally working ≥12 h a week)Experience symptoms during work or in their own opinion have problems performing their work (including absenteeism).

Patients who are unable to access and fill in the online follow-up questionnaires will be excluded.

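### Absenteeism is treated as a continuous outcome, and the fallback for non-normal data cannot analyse days off work as the plan intends

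*Protocol article*

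**What the plan says.** The Data analyses section makes one rule for every outcome: "All outcome measurements will be continuous variables and will be presented as means and standard deviations". It continues: "Between-group differences for all outcomes will be analysed using linear regression". Normality is to be checked with histograms, normal probability plots and Shapiro-Wilk tests, and then: "If data appears to be not normally distributed, Mann-Whitney U tests or log transformation will be performed". Each outcome is analysed separately at four and at eight months, "adjusted for the baseline measurement of each outcome measure".

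The Secondary outcomes section defines absenteeism as "the number of days they had been out of work due to their complaints during the previous month". It also lists the attention given to work participation and the level of satisfaction "of the patient with this attention will be measured using five-point Likert scales".

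Sick leave is not required for entry. The last inclusion criterion under Participants and recruitment reads "Experience symptoms during work or in their own opinion have problems performing their work (including absenteeism", so symptoms at work are enough.

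For baseline characteristics, the Data analyses section does separate symmetric continuous, other continuous and categorical variables. It makes no such distinction for outcomes.

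**The concern.** The blanket statement conflicts with the article's own outcome definitions. Days off work in one month is a count with a floor at zero and a ceiling at the length of the month. The entry criteria let in patients who are working with symptoms, so a pile-up at zero has to be expected. A five-point item is ordinal.

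The mislabel alone would be a matter of wording. What gives it weight is the next step. The normality check would send absenteeism to the fallback, and neither option there delivers what the same section promises. Two methods are joined by an unqualified alternative, with no rule for choosing. Because each time point is analysed separately, the method could even differ between four and eight months. At stake is the interpretability of the only outcome listed that counts days lost from work.

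**Working it through.** **1. The plan's own figure.** The article gives no sample size or expected effect for absenteeism. Its 221 per arm concerns the two primary outcomes and reproduces:
- n = 2(1.96 + 0.84)² × 1.8² / 0.7², about 104 per arm without clustering.
- Patients per practice with 15 practices and ICC 0.05: 104 × 0.95 / (15 − 104 × 0.05) = 98.8 / 9.8 = 10.08, about 10.
- 15 × 1.1 = 16.5, so 17 practices; 10 × 1.25 = 12.5, so 13 patients; 17 × 13 = 221.

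The figure is used here only to set the number analysed: 17 × 10 = 170 per arm (221 × 0.75 gives about 166).

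**2. Is the fallback triggered?** Days were simulated for 166 per arm in 2,000 runs, with assumed absence rates from 10% to 60%. Shapiro-Wilk on the residuals rejected normality in every run.

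**3. Does the fallback work for days?**
- *Log transformation.* log(0) is undefined. With zero shares of 60%, 75% or 85%, that share of patients has no transformed value. Analysing absentees only compares subsets formed after randomisation. log(1 + days) can be computed, but the plan does not state it, and it does not give a difference in days.
- *Mann-Whitney.* In its standard form it has no place for the baseline value that the plan promises for each outcome, nor for practice, although the sample size assumes an ICC of 0.05. It returns no effect in days.

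**4. Does the choice matter?** Simulation settings: 170 per arm, 1,500 runs per scenario, no clustering; days for absentees drawn from a gamma distribution (shape 0.8, scale 9), rounded up and capped at 22. Zero shares, distribution and effects are all assumptions, because the article gives none.
- Fewer absent: zero share rises from 60% to 74%, 75% to 87%, or 85% to 94% (mean days 2.89 to 1.88, 1.79 to 0.94, 1.08 to 0.43).
- Shorter absences only: the scale falls to 0.4, 0.3 and 0.3 of its control value.

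| Effect | Zero share, control | Linear regression | Mann-Whitney | log(1 + days) | Logistic, any absence |
|---|---|---|---|---|---|
| Fewer absent | 60% | 0.495 | 0.769 | 0.728 | 0.810 |
| Fewer absent | 75% | 0.545 | 0.787 | 0.741 | 0.809 |
| Fewer absent | 85% | 0.557 | 0.777 | 0.740 | 0.790 |
| Shorter only | 60% | 0.951 | 0.191 | 0.617 | not run |
| Shorter only | 75% | 0.935 | 0.096 | 0.544 | not run |
| Shorter only | 85% | 0.681 | 0.058 | 0.305 | not run |

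Mann-Whitney leads linear regression by 0.22 to 0.27 when fewer are absent (0.777 − 0.557; 0.769 − 0.495). It trails by 0.62 to 0.84 when absences shorten (0.681 − 0.058; 0.935 − 0.096).

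A second generator (166 per arm; days for absentees 1 plus a negative binomial with mean 7 and size 0.8, capped at 22) shows the same reversal. With absence falling from 20% to 10%, power is 0.49 for mean days, 0.72 for Mann-Whitney and 0.72 for any absence. With the mean parameter cut from 7 to 3 and the absence rate unchanged, mean days has 0.48 (20% absent) and 0.67 (30% absent), and any absence 0.05 in both.

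**5. Is linear regression invalid for days?** No. With no true effect and no clustering, its rejection rate was 0.057, 0.050 and 0.045 at the three zero shares. With an ICC of 0.05 present and ignored, every method tried rose to about 0.07 to 0.11.

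**6. Likert items.** Comparing mean scores against Mann-Whitney, with 170 per arm: type I error 0.048 against 0.051, and power 0.717 against 0.717.

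**The case against.** The plan does foresee non-normal data, and one of its two fallbacks, Mann-Whitney, performs about as well as comparing any absence when the intervention changes only who is absent. Linear regression on days keeps its error rate and estimates the quantity that most readers want, the mean difference in days. The analysis is also to be done blind to allocation, which limits the scope for picking a method to favour an arm. All of this stands. It does not settle which quantity will be estimated, and Mann-Whitney is nearly blind to shorter leave.

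A reader might infer that linear regression on days is inefficient in general. The documents do not support that. The article's Abstract and Discussion expect fewer or shorter absences, and the ranking of methods reverses between the two. For the same reason, making any absence the main estimate would miss shorter leave.

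A reader might also infer that a cost result depends on this analysis. Lower costs are stated as an expectation, and the article describes no cost analysis that uses absenteeism.

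Finally, "the number of physical therapy treatment sessions, recurrences of complaints and referrals to other occupational health professionals" are listed among other measures, outside the primary and secondary outcomes. They do not clearly fall under the blanket statement, and their models may be left to an analysis plan.

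**Conclusion.** The point holds for absenteeism. The statement that all outcomes are continuous contradicts the outcome list, and the fallback that would then apply fails as written: one option is undefined at zero, the other drops the baseline adjustment and practice and gives no effect in days, and nothing fixes the choice before the data are seen. How much this matters depends on unknowns. Under the assumed zero shares, power with Mann-Whitney ranges from 0.06 to 0.79 according to whether leave becomes shorter or less frequent. These figures illustrate sensitivity to the choice; they are not an estimate of power lost in this trial.

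For the Likert items the fault is a mislabel with negligible practical effect. The primary outcomes and the sample size are untouched. Severity is minor to moderate.

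**What to change.** In the Data analyses section:
- Replace the sentence calling all outcomes continuous with a short classification by type: scores, count of days, ordinal items.
- Remove the Mann-Whitney or log fallback for absenteeism.
- Name one main analysis of days, the same at four and eight months, that handles zeros and includes baseline days and practice. Either a negative-binomial mixed model with a random practice intercept, or a mean difference in days with cluster-robust or bootstrap intervals, would serve; one must be chosen in advance.
- Add any absence, by a logistic mixed model, as a supporting analysis and not as the main estimate.
- Report the percentage with any absence alongside mean and median days.
- Let the Likert items stay as mean scores or be analysed as ordinal, stating which.

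The cost is wording, a little extra analysis, and a check that the named software fits the chosen model. No new data and no change to the sample size are needed.
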